### Outcomes

The primary outcome is LBP severity (average intensity of LBP over the past week, assessed using the 0–10 NRS) at 3 months post-randomisation. Secondary outcomes will be collected up to 2 years after randomisation and include:

Functional disability is measured using the Oswestry Disability Index^28^ version 2.1b.HRQoL was measured using the EuroQol 5-dimension five-level questionnaire (EQ-5D-5L).^29^General health is measured using the 12-Item Short Form Survey (SF-12) Physical Component Score.^30^Mental health is measured using the SF-12 Mental Component Score.Time to pain recovery: time from randomisation until the participant first reports a pain reduction of ≥60% that remains at ≥60% lower than baseline at their next assessment.Uptake of offer of alternative treatment (ie, blinded cross-over to RFD/placebo) after 3 months.Satisfaction with treatment outcome using a Likert scale.Adverse health events.Work outcomes were assessed using the Work Productivity and Activity Impairment (WPAI) questionnaire.^31^Resource use assessed via a patient-reported resource use questionnaire.

### Data collection

Screening data will be collected before consent to establish patient eligibility. Some demographic data (see online supplemental file), information about pain severity and duration of current LBP episode will also be collected from participants and non-participants, as far as possible, at the time of screening, to characterise the population and to interpret the applicability of the trial findings to the reference population. The schedule of data collection outlined in online supplemental table 1 will take place after consent has been received. Data will either be collected on paper data collection forms and entered into the study database or entered directly into the database. Data for the primary outcome and most secondary outcomes will be collected via patient-completed questionnaires. Participants will be followed up at 2, 4, 6, 8 and 10 weeks for pain severity, as well as HRQoL at 6 weeks and adverse health events at 2 and 6 weeks. After this, participants will complete postal/online questionnaires at 3, 6, 12, 18 and 24 months. The participant’s time in the study will end after they have completed the follow-up at 24 months post-randomisation. The end of the study as a whole will be after all participants have completed the follow-up, all data queries have been resolved, the database locked and the analysis completed.

### Sample size

A sample size of 250 participants (125 per group) is sufficient to detect a difference of at least 0.84 in the pain severity NRS (scored 0–10) between randomised groups with 90% power and 5% two-tailed significance, assuming:

The SD for the pain NRS is 2.0 (17).Correlation between NRS at baseline and 3 months is 0.3 (based on data from the MINT trials provided by collaborator [name]).Allowing for up to 10% attrition at 3 months.

The trial will, therefore, have sufficient power to detect the target difference used by NICE (1-point difference) and reflect a moderate effect size.^32^

### Statistical analyses

The data will be analysed on an intention-to-treat basis and will follow a prespecified statistical analysis plan.

The primary outcome (NRS) will be analysed using linear mixed effect models, including all available repeated pain measurements up to 3 months, adjusted for time point and the treatment×time point interaction as fixed effects, and operator and participant as random effects. Treatment effects at 3 months will be reported with 95% confidence interval. Protocol deviations will be documented, and a per-protocol secondary analysis will be considered if there are a substantial number of protocol deviators. A secondary responder analysis of the primary outcome will be performed, exploring the between-group difference in the proportion of participants achieving ≥30% improvement in pain from baseline as recommended by the Initiative on Methods, Measurement and Pain Assessment in Clinical Trials,^33 34^ and the number needed to treat will be calculated based on this analysis.^35^,^37^

Continuous and binary secondary outcomes will also be compared using mixed models; and if the treatment×time point interaction is significant at the 10% level, treatment effects at 3, 6, 9, 12, 18 and 24 months will be reported. Time to pain recovery will be analysed using survival methods. Frequencies of adverse events will be described. Missing data on patient questionnaires will be dealt with according to the scoring manuals. Imputation methods, for example, multiple imputation, will be considered if the proportion of missing data is >5%, otherwise complete-case analysis will be undertaken.

Subgroup analyses for the primary outcome will be analysed by adding a treatment by subgroup interaction to the model. Subgroups include younger versus older age (split at median); sex; lower versus higher (split at median) index of multiple deprivation; isolated versus widespread pain; ≥80% reduction in NRS vs ≥60%–79% reduction in NRS in response to the MNBB; low/medium versus high risk of persistent disabling pain based on the STarT Back tool.^38^

Exploratory analyses will assess the effect of reintervention with the alternative treatment using methods developed to appropriately adjust for treatment switching.^39^ Exploratory analyses will also be undertaken to assess the learning effect of the intervention for those less experienced practitioners with fewer than 20 procedures by including procedure numbers in the model. Screening data will be compared descriptively between randomised and non-randomised patients, to ascertain generalisability of results. No formal interim analysis is planned.

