### Randomisation and blinding

Randomisation of eligible participants will be performed using a secure internet-based randomisation system, ensuring allocation concealment. Participants will be allocated in a 1:1 ratio to either RFD or placebo. A computer-generated allocation sequence will be prepared by an independent statistician, using random permuted blocks of varying size and stratified by the operator to ensure that any operator effect is distributed equally across groups.

Participants, their clinical care team and the local research team will not be informed of the allocation. Radiofrequency machines to be used in the trial will have to meet key criteria, including having an appropriate method for maintaining blinding of the clinical team and the participant. The trained randomiser will randomise the participant and then control the electrode temperature. The machine display (showing the temperature) will not be visible to the rest of the team in the theatre. This person will have no other role in the trial. Treatment allocation will only be unblinded on participant request or if clinically indicated; for example, in the event of a serious adverse event requiring knowledge of the allocation for treatment. The success of blinding will be assessed using the Bang Blinding Index.^25^

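### The sample size relies on a 0.3 baseline-to-3-month correlation, but the primary model as listed has no baseline NRS term; the power cost is modest and the remedy is one sentence

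*Protocol article*

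**What the plan says.** The Sample size section of the protocol article states: "A sample size of 250 participants (125 per group) is sufficient to detect a difference of at least 0.84", "with 90% power and 5% two-tailed significance". It lists three assumptions. The first is "The SD for the pain NRS is 2.0", the second is "Correlation between NRS at baseline and 3 months is 0.3", and the third is attrition of up to 10% at 3 months. It then says that power is also sufficient for a 1-point target difference.

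The Statistical analyses section describes the primary analysis as a linear mixed model on all available repeated pain scores up to 3 months, "adjusted for time point and the treatment×time point interaction as fixed effects, and operator and participant as random effects". It reports the treatment effect at 3 months. It does not mention baseline NRS as a covariate, and it does not say whether baseline counts among the repeated scores. It refers to a prespecified analysis plan, which is not shown.

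The Cost-effectiveness analyses section does name adjustment for baseline EQ-5D-5L. The Data collection section places pain assessments at 2, 4, 6, 8 and 10 weeks and at 3 months.

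**The concern.** A baseline-to-outcome correlation reduces the required sample size only when the analysis conditions on baseline. Under ANCOVA the residual variance is multiplied by 1 − r². The listed model has no such term.

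Repeated post-randomisation scores are not a substitute. With a free treatment effect at each time point and complete data, the 3-month contrast is, apart from the operator term, simply the difference in 3-month means. The earlier visits add information about the 3-month contrast only through participants whose 3-month score is missing.

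The stated power therefore belongs to an analysis that the article does not describe. What is at stake is some precision on the single primary contrast, and agreement between the design calculation and the analysis.

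**Working it through.** **Inputs, all from the protocol article.** N = 250. Allocation: "Participants will be allocated in a 1:1 ratio to either RFD or placebo". Difference 0.84, power 90%, two-sided 5%, SD 2.0, r = 0.3, attrition 10%. Evaluable per arm: 125 × 0.9 = 112.5. Normal quantiles: 1.960 + 1.282 = 3.242.

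**1. Reproducing the plan's figure with baseline adjustment.**
- Residual SD = 2.0 × √(1 − 0.3²) = 1.908.
- n per arm = 2 × 1.908² × 3.242² / 0.84² = 108.4, rounded up to 109.
- After attrition: 109 / 0.9 = 121.1, rounded up to 122 per arm, 244 in total.

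The stated 250 covers this with a small margin.

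**2. The same calculation without baseline adjustment.**
- n per arm = 2 × 2.0² × 3.242² / 0.84² = 119.1, rounded up to 120.
- After attrition: 120 / 0.9 = 133.3, rounded up to 134 per arm, 268 in total.

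This exceeds 250. If rounding is left to the end, the two totals are 241 and 265, with the same conclusion.

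**3. Detectable difference and power at 112.5 per arm.** The standard error is SD × √(2/112.5) = SD × 0.1333. The difference detectable with 90% power is 3.242 × SE. Power is Φ(difference/SE − 1.960).

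| Analysis at 3 months | SE | Detectable at 90% | Power at 0.84 | Power at 1 point |
|---|---|---|---|---|
| Baseline-adjusted | 0.254 | 0.825 | 91.0% | 97.6% |
| Unadjusted | 0.267 | 0.864 | 88.3% | 96.3% |

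Using the noncentral t distribution, power at 0.84 is 90.8% and 88.0%.

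**4. Allowing for the repeated-measures model.** This is a generalised least squares calculation with 125 per arm and six post-randomisation visits. It takes SD 2.0 at every visit, and 10% missing at 3 months but present at all earlier visits. The correlation between follow-up visits is not in the article, so a range is assumed.

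| Assumed between-visit correlation | Power at 0.84, post-randomisation scores only | Power at 0.84, baseline as response with common arm mean |
|---|---|---|
| 0.3 | 88.9% | 91.4% |
| 0.5 | 89.6% | 92.0% |
| 0.7 | 90.3% | 92.6% |
| 0.8 | 90.6% | 92.9% |

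The missing-data pattern is favourable to the model. If those missing at 3 months had also missed earlier visits, less would be recovered and the first column would move back towards 88.3%. At every assumed correlation, using baseline adds about 2 to 2.5 percentage points.

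**The case against.** The strongest reply is that this is a condensed article that defers to an analysis plan. Its model sentence is not exhaustive, since it does not list a treatment main effect either. Baseline adjustment may well be in the plan, and the wording about all available repeated scores may be meant to include baseline as a response. With a common baseline mean, that would deliver more than the stated power. Part of this stands: the article does not show that the final analysis will ignore baseline. But it does spell out the fixed and random effects of its primary model, and it names baseline adjustment for the economic analysis. The two sections as printed do not match.

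The second reply is that little turns on it. That largely stands. The unadjusted estimate is unbiased under randomisation, its standard error already allows for chance baseline imbalance, and at r = 0.3 adjustment removes only 9% of the variance.

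Three stronger readings are tempting, and the article does not support them:
- **The trial is underpowered.** The lowest figure for the unadjusted 3-month contrast is about 88% against 90%, and power at the 1-point target is at least 96%.
- **The 3-month effect is a change-from-baseline contrast with much lower power.** The article speaks of treatment effects at 3 months and states no change-score contrast. The size of any loss would also depend on the baseline SD, which is not given separately.
- **The participant random effect inflates the type I error.** That depends on how SDs or correlations vary across visits, which the article does not report. A participant random effect does not exclude further residual structure, and covariance structure and degrees-of-freedom methods are normally left to the analysis plan.

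**Conclusion.** The point holds as an inconsistency of modest size. In the single-time-point calculation, 250 participants give 90% power at 0.84 only with baseline adjustment (244 needed, against 268 without), and the primary model as listed does not include it. The cost is about 91% power falling to about 88%. It falls to about 89% to 91% if repeated measures recover part of the loss.

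The first two figures use only the article's inputs. The last range rests on assumed between-visit correlations of 0.3 to 0.8, a constant SD, and dropout confined to the 3-month visit. Power for the 1-point target is not in doubt.

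The reason to act is that precision is available from data already collected and the remedy has no real downside. It is not that the trial would otherwise fail.

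**What to change.** Amend the primary model in the protocol, and check that the analysis plan agrees, in one of two ways:

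1. Keep the post-randomisation scores at weeks 2, 4, 6, 8 and 10 and month 3 as responses, and add baseline NRS and baseline NRS×time point as fixed effects alongside the terms already listed.
2. Include baseline as a response, with the two arms' baseline means constrained equal. In that case, use a within-participant covariance that does not force the baseline-to-follow-up correlation to equal the between-visit correlation. A lone participant random intercept would force them equal. The article puts the baseline-to-3-month correlation at 0.3 and gives no between-visit value.

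Either option brings the analysis into line with the basis of the sample size. The cost is one sentence and, for option 1, six extra fixed-effect parameters (one for baseline, five for its interaction with six time points). No new data are needed, because the 30% responder analysis already requires a baseline pain score. The article reports 47 participants randomised as of 8 February 2024, with recruitment continuing, so on that timetable the model could be settled well before analysis.

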**Methods and analysis:**

RADICAL (RADIofrequenCy denervAtion for Low back pain) is a double-blind, parallel-group, superiority randomised controlled trial. A total of 250 adults listed for RFD will be recruited from approximately 20 National Health Service (NHS) pain and spinal clinics. Recruitment processes will be optimised through qualitative research during a 12-month internal pilot phase. Participants will be randomised in theatre using a 1:1 allocation ratio to RFD or placebo. RFD technique will follow best practice guidelines developed for the trial. Placebo RFD will follow the same protocol, but the electrode tip temperature will not be raised. Participants who do not experience a clinically meaningful improvement in pain 3 months after randomisation will be offered the alternative intervention to the one provided at the outset without disclosing the original allocation. The primary clinical outcome will be pain severity, measured using a pain Numeric Rating Scale, at 3 months after randomisation. Secondary outcomes will be assessed up to 2 years after randomisation and include disability, health-related quality of life, psychological distress, time to pain recovery, satisfaction, adverse events, work outcomes and healthcare utilisation. The primary statistical analyses will be by intention to treat and will follow a prespecified analysis plan. The primary economic evaluation will take an NHS and social services perspective and estimate the discounted cost per quality-adjusted life-year and incremental net benefit of RFD over the 2-year follow-up period.

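### A 10% interaction test decides whether 3-month secondary effects are shown, although crossover after 3 months is built into the design; the listed 9-month effect has no assessment behind it

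*Protocol article*

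**What the plan says.** Under Statistical analyses, secondary outcomes get the same type of model as the primary: "Continuous and binary secondary outcomes will also be compared using mixed models". The reporting rule follows: "if the treatment×time point interaction is significant at the 10% level, treatment effects at 3, 6, 9, 12, 18 and 24 months" are to be reported. The section does not say what is reported when the interaction is not significant.

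The Data collection section sets the schedule. Before 3 months: "Participants will be followed up at 2, 4, 6, 8 and 10 weeks for pain severity, as well as HRQoL at 6 weeks". After that: "participants will complete postal/online questionnaires at 3, 6, 12, 18 and 24 months". No 9-month contact appears.

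The abstract describes the crossover: "Participants who do not experience a clinically meaningful improvement in pain 3 months after randomisation will be offered the alternative intervention". This applies to both arms, and the Outcomes section lists uptake of the offer after 3 months as an outcome in its own right.

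The primary outcome is handled differently. Its model uses pain scores up to 3 months only, and the 3-month effect with its 95% CI is reported without any condition. Adjustment for switching is planned, but as an exploratory analysis.

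**The concern.** The Introduction states the trial's aim as RFD against placebo, and its second objective is the between-group difference in disability, quality of life, psychological distress and other secondary outcomes. Once non-improvers can take the other treatment, the arms no longer differ simply in RFD versus placebo. They differ in which treatment came first.

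The design therefore makes a change in the contrast after 3 months likely. A rule that shows visit-specific effects only when a test detects that change leaves a data-driven pre-test to decide whether the 3-month effect on disability or the SF-12 scores is seen at all. A non-significant interaction is weak evidence of a constant effect, because the trial was sized for the primary comparison and not for this test.

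Separately, an effect is promised at a time when no questionnaire is scheduled.

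**Working it through.** **1. Visit list.** Statistical analyses lists six times: 3, 6, 9, 12, 18 and 24 months. Data collection lists five: 3, 6, 12, 18 and 24 months. Month 9 is the only mismatch.

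**2. Visits before and after crossover.** Of the five scheduled questionnaires, one (3 months) precedes crossover and four (80%) follow it. Quality of life also has a 6-week measurement before crossover.

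**3. The plan's own figure.** Inputs from Sample size: difference 0.84, SD 2.0, baseline correlation 0.3, 90% power, two-sided 5%, 10% attrition.
- Adjusted SD = 2.0 × √(1 − 0.3²) = 1.908.
- n per arm = 2 × (1.960 + 1.282)² × 1.908² / 0.84² ≈ 108.4, so 109.
- 109 / 0.9 = 121.1, so 122 per arm and 244 in total, against 250 stated.

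The stated size is reproduced within 3% and is not in dispute. After 10% attrition about 112 per arm are analysed (125 × 0.9 = 112.5). The target effect is 0.84 / 2.0 = 0.42 SD.

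**4. Size of the averaged effect.** The documents give no switching rate, so what follows is assumed. A share s of the placebo arm switches after 3 months and gains the full RFD effect by 6 months; the effect otherwise persists; the five visits have equal weight. The later contrast is then (1 − s) of the 3-month contrast, and the average keeps [1 + 4(1 − s)] / 5 of it:
- s = 0.25: (1 + 3.00) / 5 = 0.80
- s = 0.42: (1 + 2.32) / 5 = 0.66
- s = 0.63: (1 + 1.48) / 5 = 0.50

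**5. Power of the 10% interaction test.** This is a 4-df Wald test over five visits, with n = 112 per arm at every visit, 3-month effect d (in SD units) and exchangeable between-visit correlation ρ. The noncentrality is

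λ = (n / 2) × (d·s)² × 0.8 / (1 − ρ),

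referred to a noncentral chi-square with critical value 7.78. Example: d = 0.42, s = 0.25, ρ = 0.5 gives λ = 56 × 0.105² × 0.8 / 0.5 = 0.99 and power 18%.

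| Placebo switching | Share of 3-month effect kept | Power, d = 0.42 (ρ = 0.5 / 0.7) | Power, d = 0.50 (ρ = 0.5 / 0.7) |
|---|---|---|---|
| 25% | 80% | 18% / 24% | 22% / 30% |
| 42% | 66% | 34% / 50% | 44% / 64% |
| 63% | 50% | 62% / 83% | 77% / 94% |

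The gate thus stays shut in 70–82% of trials at 25% switching, 36–66% at 42% and 6–38% at 63%.

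**6. Sensitivity to the correlation.** If later effects are half the 3-month effect (d = 0.42), power is 34%, 44% and 64% at ρ = 0.3, 0.5 and 0.7. With serial correlation of 0.7 per six months it is 71%.

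**7. What the 3-month contrast can show.** Without baseline adjustment its standard error is √(2 / 112.5) = 0.133 SD, and power for 0.42 SD is 88%. The five-visit average has a standard error of 0.133 × √[(1 + 4ρ) / 5], which is 0.103 at ρ = 0.5 and 0.116 at ρ = 0.7. The 3-month interval is therefore about 15–29% wider than that of the average.

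**The case against.** Several stronger readings are tempting, and the article does not support them.

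- **That the plan pools 3 to 24 months as its headline secondary result.** It never says so. Only the significant branch is written down, and an analysis plan that is not shown may complete the rule. Averaging is the natural implication, no more. What stands is that the written rule makes no unconditional promise of a 3-month secondary effect.
- **That the averaged effects are biased.** The trial is pragmatic and analysed by intention to treat. Comparing arms as randomised, with optional switching, is a legitimate treatment-policy effect. It is diluted only relative to RFD versus placebo, and only if switching narrows the gap between arms.
- **That 3 months is the only measurement before crossover.** Quality of life is also measured at 6 weeks. The Cost-effectiveness analyses section also commits to cost per QALY at 3 months without any gate, so EQ-5D information before crossover does not depend wholly on the interaction test.
- **That time to pain recovery has the same fault.** Its definition is "time from randomisation until the participant first reports a pain reduction of ≥60% that remains at ≥60% lower than baseline at their next assessment", and the article is silent on reintervention. Censoring rules are commonly left to the analysis plan. Ending follow-up at 3 months would also clash with the confirmation rule, because a recovery first reported then can be confirmed only at 6 months. No finding is made on this outcome.

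The illustration can also be challenged fairly. The switching rates are assumed. Placebo switchers are selected for not improving and may gain less than the full effect, and RFD's effect may wane. Where dilution is worst (63% switching), the gate usually opens; the misses are concentrated where 66–80% of the effect is kept. This limits the harm but does not justify the gate.

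**Conclusion.** Two points hold.

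The 9-month effect is wrong as written: on the stated schedule there is nothing from which to estimate it.

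The interaction gate suits this design poorly, and removing it is a cheap improvement rather than an essential correction. It lets a test with 18–64% power at 25–42% switching decide whether the 3-month RFD-versus-placebo effect on secondary outcomes appears, when an unconditional 3-month contrast would have about 88% power at 0.42 SD. These figures rest on assumed switching rates, full and lasting benefit in placebo switchers, about 112 per arm at every visit, exchangeable correlation of 0.5–0.7, and a secondary effect of 0.42–0.5 SD. They show what could happen and do not predict what will. The counts of visits before and after crossover do not depend on these assumptions.

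A reader might infer that the trial's main conclusion is at risk. It is not: the primary outcome uses data up to 3 months, its effect is always reported, and the sample size is unaffected.

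**What to change.** - Drop the interaction test as a condition for reporting.
- For every secondary outcome measured at 3 months, report the 3-month effect with its 95% CI as the RFD-versus-placebo comparison, as the plan already does for pain.
- Report 6, 12, 18 and 24 months separately, labelled as effects of initial allocation with optional switching. An average over follow-up may be added as a supplement under the same label.
- Reconcile the visit list with the Data collection section by deleting the 9.

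The cost is wording in the protocol and analysis plan, more estimates to report, and somewhat wider intervals than an average would give (about 15–29% under the assumptions above). No new data are needed. The change should be made before any unblinded analysis, so that the choice of which effects to show cannot look driven by the results.
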